**Methods and analysis:**

The protocol outlines a double-center, randomized, and controlled trial design where both patients and assessors are blinded to the intervention being administered. The duration of the trial’s therapeutic intervention will span 4 weeks, followed by a 2-month observation period for monitoring any subsequent effects or outcomes. The 124 qualified individuals will be randomly allocated in a balanced 1:1 ratio to either the EA group or the drug group. All variables will undergo evaluation at the start of the study (week 0, baseline), during the treatment period at weeks 2 and 4, and during the follow-up period at weeks 8 and 12. The primary outcome is the Visual Analog Scale (VAS). Secondary outcomes include the Brief pain inventory-Facial scale (BPI-Facial), Pittsburgh Sleep Quality Index Scale (PSQI), Self-rating depression scale (SDS), Hamilton depression scale (HAMD), and Quality of Life Rating Scale (SF-36). The occurrence of any adverse reactions will be monitored and assessed throughout the duration of the trial.

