## Introduction

Postherpetic neuralgia (PHN) refers to a type of pain that persists for a duration of 1 month or longer, following the healing of an acute herpes zoster (HZ) rash (1). Epidemiological studies have shown that the occurrence rate of HZ in Europe, North America and the Asia Pacific region stands at 5 to 6 cases per 1,000 individuals per year and up to 30% of HZ patients develop PHN (2, 3). In China, the rate of PHN incidence is rising steadily each year, and the incidence increases with age (4). Clinical studies have found that PHN occurs mostly in the elderly, where the occurrence rate of PHN among patients aged over 50 can reach as high as 60 to 75%, which has a significant impact on both physical and mental well-being, as well as the overall quality of life (5, 6).

PHN, as a pain disorder that severely affects the quality of human life, faces many clinical challenges. One of the most problematic issues is the treatment of cephalo-facial PHN in patients aged 50 and above. The clinical challenges of cephalo-facial PHN in patients over 50 years of age are more daunting (7, 8), making the clinical symptoms of cephalo-facial PHN in patients over 50 years of age more complex and more difficult to treat. Therefore, this project will focus on patients over the age of 50 with cephalo-facial PHN for research.

Currently, the main clinical treatment options for PHN include drug therapy (9–11) and surgical treatment (12, 13) and alternative medicine (14, 15). Pregabalin has proven efficacy in the treatment of PHN (16) and is classified as a first-line clinical medication by guidelines (17); therefore, this study will use pregabalin as a control to investigate the clinical efficacy and safety of EA in patients with PHN. However, all of these treatment options have limitations. Studies have shown that 81.82% of patients with PHN still suffer from a similar degree of pain as before treatment, and their probability of adverse drug reactions is as high as 42.74% (18, 19). Although surgical treatment is effective for PHN, there is a greater risk of irreversible damage to the nerves and complications for patients over 50 years of age with cephalo-facial PHN (20). Therefore, there is an urgent need for alternative approaches to explore simpler, more convenient, effective, and inexpensive treatment options in the clinical treatment of cephalo-facial PHN over 50 years of age.

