### Sample size estimation

This research involves a randomized controlled trial design, where eligible participants will be allocated to two distinct groups in an equal proportion of one participant to another (1:1 ratio), and the primary outcome metric is the percentage of cases with a pain intensity VAS ≤ 2 points after 4 weeks of treatment. According to the project team’s pre-efficacy observation pre-trial, the effective rate of this study’s treatment regimen in treating PHN is about 91%, and the literature reported that the effective rate of pregabalin is 74.4% (49). The estimation of the required sample size formula for the test of superiority of the independent sample rate of two groups is used for the calculation, taking *α* = 0.025 and *β* = 0.2, with the same number of sample cases between the groups, and using a one-sided test, taking into account a 20% dropout rate. Each group will necessitate a minimum of 62 cases, resulting in a combined total of 124 cases across the two groups.

$$N=\frac{2{\left[Z_{\alpha /2}\sqrt{2\bar{p}\bar{q}}+Z_{\beta }\sqrt{p_{0}q_{0}+p_{1}q_{1}}\right]}^{2}}{{\left(p0-p1\right)}^{2}}$$

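### The sample size names VAS ≤ 2 at week 4 as the endpoint but uses undefined effective rates, so 80% power is not shown for that endpoint; even at those rates, 62 per arm gives about 69% and 49 evaluable about 59%

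*Protocol article*

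**What the plan says.** Protocol article, Sample size estimation: "the primary outcome metric is the percentage of cases with a pain intensity VAS ≤ 2 points after 4 weeks of treatment". The next sentence supplies the planning rates of 91% for electroacupuncture (EA), from the team's own pre-trial observation, and 74.4% for the control, from a cited source: "the effective rate of this study’s treatment regimen in treating PHN is about 91%, and the literature reported that the effective rate of pregabalin is". The section sets α = 0.025 one-sided, β = 0.2, 1:1 allocation and 20% dropout, and arrives at 62 per group, 124 in all. No superiority margin is stated.

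The term effective rate is not defined there or elsewhere in the article. The abstract, the primary outcome section and the Discussion all name VAS as the primary outcome without the ≤ 2 threshold.

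The Introduction, after "However, all of these treatment options have limitations", reports that "81.82% of patients with PHN still suffer from a similar degree of pain as before treatment", and pairs this with an adverse drug reaction rate.

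**The concern.** For a binary endpoint, power depends on the absolute success rates of that endpoint in both arms. A pre-trial and a published study may each call a patient effective on their own criterion, such as a percentage reduction, a category shift or any improvement, and at their own time point. VAS ≤ 2 is a demanding absolute cut-off. Entry requires a facial pain score of at least 4; if that score is on the same 0–10 scale (an assumption), VAS ≤ 2 means a fall of at least half even for the mildest eligible patient. The primary outcome section also groups scores up to 3 as mild, so the cut-off is stricter than mild pain.

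If the rates belong to another definition, the planned power describes a different endpoint. A non-significant result could then be read as evidence against an effect that the trial was never shown able to detect. The Introduction's figure of 81.82% with similar pain after treatment adds to the doubt about a 74.4% control success rate.

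**Working it through.** **Inputs** (all from Sample size estimation): p1 = 0.91, p0 = 0.744, difference d = 0.166, one-sided α = 0.025 (z = 1.95996), β = 0.2 (z = 0.8416), dropout 20%. Margin taken as 0 because none is stated. One-sided 0.025 has the same critical value as the two-tailed 0.05 in the Statistical analysis section.

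**Step 1: the plan's own figure.** The per-arm form of the printed formula is

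n = [z_α √(2 p̄ q̄) + z_β √(p0q0 + p1q1)]² / d²

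- p̄ = (0.91 + 0.744)/2 = 0.827; 2 × 0.827 × 0.173 = 0.28614; square root 0.53492
- p0q0 + p1q1 = 0.744 × 0.256 + 0.91 × 0.09 = 0.27236; square root 0.52189
- n = (1.95996 × 0.53492 + 0.8416 × 0.52189)² / 0.166² = 1.48765² / 0.027556 = 80.3, so 81 evaluable per arm
- With dropout: 81/0.8 = 101.25, so 102 per arm, 204 in all

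The stated 62 is not reproduced. A continuity correction gives 92 (115 with dropout). Reading the printed Z_α/2 with α = 0.025 gives 98 (123 with dropout). The nearest results to 62 need one-sided α = 0.05 with no dropout allowance (61.1 unpooled, 64 pooled after rounding up), and those are not the stated inputs.

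**Step 2: power of the planned size if both rates are taken as VAS ≤ 2 rates.**

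Power = Φ[(d√n − z_α × 0.53492) / 0.52189], with z_α × 0.53492 = 1.04843

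- n = 62: (0.166 × 7.8740 − 1.04843)/0.52189 = 0.496, power 69%
- n = 49 (62 × 0.8 = 49.6, whole patients): (0.166 × 7 − 1.04843)/0.52189 = 0.218, power 59%

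The second figure is the relevant one if dropout is as planned, because the Elimination criteria remove withdrawn and lost patients from the final analysis. At a 74.4% control rate with 49 per arm, even a 20-point difference has 78.8% power, so the smallest difference detectable with 80% power is slightly above 20 points, against the 16.6 planned.

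**Step 3: if the VAS ≤ 2 control rate is not 74.4%.** Every control rate below other than 74.4% is an assumption. Power is for 49 per arm at one-sided 0.025, holding one planned effect measure at a time: risk difference 0.166, rate ratio 0.91/0.744 = 1.22, or odds ratio (0.91/0.09)/(0.744/0.256) = 3.48.

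| Control rate | Same difference | Evaluable per arm for 80% (same difference) | Same rate ratio | Same odds ratio |
|---|---|---|---|---|
| 74.4% (stated) | 59% | 81 | 59% | 59% |
| 60% | 42% | 123 | 29% | 76% |
| 50% | 38% | 138 | 20% | 82% |
| 40% | 37% | 142 | 14% | 86% |
| 30% | 39% | 134 | 10% | 86% |
| 18.2% | 46% | 110 | 7% | 79% |

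The range is 7% to 86%. It shows how strongly power depends on the missing rates; it does not show which way any error runs.

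**The case against.** The strongest reply is that the two rates follow directly after the VAS ≤ 2 metric, so a reader may take effective to mean exactly that metric, with the definition set out in the full protocol that this article condenses. This stands in part. The text does not exclude that both rates were counted as VAS ≤ 2 at week 4, so one cannot say that they measure something else, only that they are not shown to measure this. It does not rescue the power statement: under this most favourable reading, Step 2 gives 69% or 59%, not 80%.

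A reader might also infer that the article contradicts itself: if 81.82% have pain similar to before treatment, VAS ≤ 2 success on pregabalin could not exceed 100 − 81.82 = 18.18%, about a quarter of the assumed 74.4%. The documents do not support this. The 81.82% is given for patients with PHN, after a remark covering drug, surgical and alternative treatment. It names no drug, dose, time point or threshold, and it cites different sources from the 74.4%. The same paragraph says that pregabalin has proven efficacy. The cap would also need the entry score to be on the VAS scale. The two figures are in unexplained tension, and no more than that.

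Finally, the sensitivity range does not establish harm from a mismatch, since power could be lower or higher than at the stated rates. That is correct. The shortfall at the stated rates is a matter of arithmetic and separate from any mismatch.

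**Conclusion.** The point holds in two parts. First, the planning rates of 91% and 74.4% are not tied to VAS ≤ 2 at week 4, so the 80% power is not shown to apply to the endpoint named for sizing. The size and direction of any error from this source are unknown. Second, if both rates are accepted as VAS ≤ 2 rates, power is about 69% with 62 per arm and about 59% with 49 evaluable; 80% needs 81 evaluable per arm, or 102 enrolled.

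This rests on a two-proportion normal approximation with pooled variance under the null, a zero margin and 20% loss. It also takes VAS ≤ 2 as the primary endpoint, as the sample size section does, although the other sections name VAS without that threshold. The 81.82% figure needs explaining but does not bound the control rate.

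**What to change.** In Sample size estimation:

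1. Give both rates on the VAS ≤ 2, week 4 definition, with source and number of patients. For EA, re-count the pre-trial data if week-4 VAS was recorded. For pregabalin, give a rate on the same cut-off. Where that is not possible, state that the cited rate uses another definition and what it is.
2. Replace the 80% with the actual power, or the smallest detectable difference, of the fixed 124 patients, before and after 20% dropout: at the stated rates, and over a plausible range of control rates marked as assumptions.

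In the Introduction, state which treatment and population the 81.82% concerns, and how it fits with the control rate used.

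The cost is a re-count of existing data, if it can be done, and a rewritten paragraph. No extra patients are needed. The downside is that the stated power becomes less favourable, or becomes a range.

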### Statistical analysis

The statistical analysis of the data will be independently conducted by a third-party statistician, unaffiliated with the pre-test phase, utilizing the SPSS 25.0 software. Measurements are described as mean ± standard deviation (
$\bar{x}\pm s$
), median, maximum, minimum, and quartiles, and counts are expressed as percentages (%). All hypothesis tests will be conducted using a two-tailed approach, with statistical significance being determined at a threshold of *p* < 0.05. Baseline data will be evaluated for between-group comparability with a two-tailed statistical test at the *α* = 5% level. For count data, the chi-squared test will be employed to analyze differences between groups. For measured data, the t-test will be utilized to compare groups. And for nonparametric variables, the Wilcoxon rank-sum test will be adopted to assess group comparisons. Baseline data will be compared between groups with two-tailed statistical tests at the α = 5% level. If the data conform to normal distribution and is chi-square, t-test for independent samples will be employed to compare differences between groups, whereas a paired t-test will be utilized to assess changes within the same group over time or under different conditions. The chi-square test will be used for count data, and nonparametric tests will be used for comparison of rank data and data not conforming to normal distribution. At a significance level of *α* = 0.05, a *p*-value less than 0.05 (*p* < 0.05) suggests that the observed difference is statistically significant. After all data entry and checking are completed, the statisticians will carry out the statistical analysis work in a timely manner and issue a written statistical analysis report.

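### The stated 62 per group (124 in total) does not follow from the protocol's own inputs; on the VAS ≤ 2 endpoint it gives about 60% power after the planned loss, not 80%

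*Protocol article*

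**What the plan says.** All the inputs are in the protocol article, under Sample size estimation:

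- **Endpoint:** "the primary outcome metric is the percentage of cases with a pain intensity VAS ≤ 2 points after 4 weeks of treatment".
- **Electroacupuncture rate**, from the team's own pre-trial observation: "the effective rate of this study’s treatment regimen in treating PHN is about 91" per cent.
- **Pregabalin rate:** "the literature reported that the effective rate of pregabalin is 74.4" per cent.
- **Error rates:** "taking *α* = 0.025 and *β* = 0.2".
- **Design:** a superiority comparison of two independent proportions with no margin stated, "with the same number of sample cases between the groups, and using a one-sided test, taking into account a 20% dropout rate".
- **Result:** "Each group will necessitate a minimum of 62 cases, resulting in a combined total of 124 cases across the two groups".

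The formula printed beneath uses Z(alpha/2) and carries a leading factor of 2.

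Two other sections bear on the point. Statistical analysis says "All hypothesis tests will be conducted using a two-tailed approach", with significance at p < 0.05. The note under Elimination criteria keeps patients who withdraw or are lost out of the final analyses, so dropout directly reduces the number analysed.

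**The concern.** Every input needed to recompute the figure is printed, so the result can be checked without the full protocol or a statistical analysis plan. The stated number after dropout is smaller than the number the same inputs require before dropout. Choice of variance formula or rounding cannot explain that.

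What is at stake is the 80% power claim. If the true rates are those assumed, the chance of missing the difference is about 40% rather than the stated 20%. A non-significant result would then be read as coming from an adequately powered trial when it did not.

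**Working it through.** **Inputs** (Sample size estimation): p1 = 0.91, p0 = 0.744, difference 0.166, mean rate 0.827. Z for power 0.80 is 0.8416. One-sided alpha 0.025 gives Z = 1.96, which is also the critical value of the two-sided 0.05 test in Statistical analysis.

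**Building blocks**
- √(2 × 0.827 × 0.173) = √0.28614 = 0.5349
- √(0.744 × 0.256 + 0.91 × 0.09) = √0.27236 = 0.5219
- 0.166² = 0.027556

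**Attempt to reproduce 62 from the stated inputs**

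Printed formula with Z = 1.96: N = 2 × (1.96 × 0.5349 + 0.8416 × 0.5219)² / 0.027556 = 2 × 1.4877² / 0.027556 = 160.6. Because of the leading 2 this is the total for both groups, so 80.3 per group, or 81. Read instead as a per-group figure it would be 161 per group, further from 62.

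Unpooled variance: (1.96 + 0.8416)² × 0.27236 / 0.027556 = 77.6 per group, or 78.

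Adding 20% dropout as n/0.8:
- Unpooled: 77.6/0.8 = 97.0. Rounding to 78 first gives 97.5, or 98.
- Pooled: 80.3/0.8 = 100.4. Rounding to 81 first gives 101.25, or 102.

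The requirement is therefore 97 to 102 randomised per group, 194 to 204 in total. Inflating by 1.2 instead still gives 93 to 98 per group.

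**Literal reading of the printed Z(alpha/2).** With alpha = 0.025, Z = 2.241 and the formula gives 97.4 per group, or 98. After dropout this is 97.4/0.8 = 121.7, or 98/0.8 = 122.5, so about 122 to 123 per group.

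**Routes that do reach 62.** Two were found, and each departs from the text:
- One-sided alpha 0.05, no dropout step: 61.1 unpooled (62) or 63.1 pooled (64). With dropout added to the rounded figures it becomes 78 to 80.
- Z = 2.241, pooled, with dropout: 123. If that per-group figure is mistaken for the total and halved, it gives 61.5, so 62 per group and 124.

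**Power of 62 per group** at two-sided 0.05 (equivalently one-sided 0.025). Normal approximation: power = Φ[(0.166√n − 1.96 × 0.5349)/0.5219]. The exact column enumerates the uncorrected chi-squared test.

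| Analysed per group | Normal approximation | Exact |
|---|---|---|
| 62 (no loss) | Φ(0.496) = 69.0% | 69.6% |
| 50 | Φ(0.240) = 59.5% | 62.4% |
| 49 | Φ(0.218) = 58.6% | 61.5% |

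A 20% loss from 62 leaves 62 × 0.8 = 49.6, hence the 49 and 50 rows. With the literal Z = 2.241, power at 50 per group falls to 48.1%.

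**The case against.** The arithmetic itself is hard to contest. The best case on the other side concerns how much may be concluded from it, and four limits stand.

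1. A reader might infer that the authors used one-sided alpha 0.05 and forgot the dropout allowance. That route reaches 62, but so does taking the inflated Z(alpha/2) per-group figure as the total, and there the allowance is included. Neither can be confirmed from the document.
2. A reader might blame the shortfall on the one-sided wording in Sample size estimation against the two-tailed wording in Statistical analysis. One-sided 0.025 and two-sided 0.05 share the critical value 1.96, so this is a labelling mismatch that adds nothing to the shortfall. The real inconsistency is the printed Z(alpha/2) alongside alpha 0.025 and a one-sided test.
3. The power figures belong to the VAS ≤ 2 proportion only. The Abstract, the Primary outcome measure section and the Discussion present the VAS score itself as primary. The document gives no standard deviation or expected mean difference for it, so power on the score cannot be computed.
4. For the same reason, a reader cannot rescue 124 by saying that about 50 per group is adequate for the continuous score. The documents do not support that either.

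None of these limits brings 62 within reach of the stated alpha, power and dropout.

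**Conclusion.** Wrong as written. The stated inputs require about 78 to 81 evaluable and 97 to 102 randomised patients per group (194 to 204 in total), against 62 and 124. The literal Z(alpha/2) reading widens the gap. The number is too small whether or not it contains the dropout allowance, and its origin remains unknown.

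For the VAS ≤ 2 endpoint, power is about 69 to 70% with full retention and about 59 to 62% after the planned loss, where 80% is stated. This rests on the protocol's own rates of 91% and 74.4%, a zero superiority margin, a critical value of 1.96, a loss of 20% in each group, and the exclusion of lost patients from the analysis. It does not extend to a comparison of mean VAS scores.

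**What to change.** Revise the Sample size estimation paragraph and keep 124:

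- State that 62 randomised per group with 20% loss (about 50 evaluable) gives about 60% power for 91% against 74.4% at two-sided alpha 0.05, and about 69% without loss.
- Print one convention, either Z(alpha/2) with two-sided alpha 0.05 or Z(alpha) with one-sided alpha 0.025, and make the wording agree with Statistical analysis.
- State that the formula with its leading factor 2 gives the total N, not the number per group.

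The cost is the rewording of one paragraph, with no additional patients. The drawback is that the power on record becomes less favourable. Keeping the 80% claim on this endpoint would instead mean about 70 to 80 more participants (194 − 124 to 204 − 124).

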### Statistical analysis

The statistical analysis of the data will be independently conducted by a third-party statistician, unaffiliated with the pre-test phase, utilizing the SPSS 25.0 software. Measurements are described as mean ± standard deviation (
$\bar{x}\pm s$
), median, maximum, minimum, and quartiles, and counts are expressed as percentages (%). All hypothesis tests will be conducted using a two-tailed approach, with statistical significance being determined at a threshold of *p* < 0.05. Baseline data will be evaluated for between-group comparability with a two-tailed statistical test at the *α* = 5% level. For count data, the chi-squared test will be employed to analyze differences between groups. For measured data, the t-test will be utilized to compare groups. And for nonparametric variables, the Wilcoxon rank-sum test will be adopted to assess group comparisons. Baseline data will be compared between groups with two-tailed statistical tests at the α = 5% level. If the data conform to normal distribution and is chi-square, t-test for independent samples will be employed to compare differences between groups, whereas a paired t-test will be utilized to assess changes within the same group over time or under different conditions. The chi-square test will be used for count data, and nonparametric tests will be used for comparison of rank data and data not conforming to normal distribution. At a significance level of *α* = 0.05, a *p*-value less than 0.05 (*p* < 0.05) suggests that the observed difference is statistically significant. After all data entry and checking are completed, the statisticians will carry out the statistical analysis work in a timely manner and issue a written statistical analysis report.

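### The plan names only unadjusted between-group tests although every scale is measured at baseline; the tests are valid, but a baseline-adjusted comparison would be more precise.

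*Protocol article*

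**What the plan says.** The Statistical analysis section of the protocol article names its tests one by one.

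- Between groups, continuous data: "For measured data, the t-test will be utilized to compare groups". Later in the section, if the data are normal, a "t-test for independent samples will be employed to compare differences between groups".
- Between groups, non-normal or rank data: nonparametric tests, with the Wilcoxon rank-sum test named.
- Between groups, binary data: "The chi-square test will be used for count data".
- Within each group: "a paired t-test will be utilized to assess changes within the same group over time or under different conditions".
- At baseline: "Baseline data will be evaluated for between-group comparability with a two-tailed statistical test" at the 5% level. The instruction is repeated a few lines later: "Baseline data will be compared between groups with two-tailed statistical tests at the α = 5% level".

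No ANCOVA, regression, mixed model or other baseline-adjusted method appears anywhere in the article.

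The data for such a method are collected. The abstract says "All variables will undergo evaluation at the start of the study (week 0, baseline), during the treatment period at weeks 2 and 4", then at weeks 8 and 12. Table 1 shows VAS, BPI-Facial, SDS, HAMD, PSQI and SF-36 at all five time points.

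**The concern.** A patient's pain, sleep or mood score before treatment usually predicts part of the score at week 4. A two-sample test on follow-up scores leaves that predictable part in the error term. A test on change scores subtracts the baseline in full, which over-corrects unless the correlation is high. An analysis with baseline as covariate gives it the weight that the data support. In a trial expecting about 50 evaluable patients per arm, that precision is worth having.

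Two other named analyses do not fill the gap. The paired t-tests ask whether each arm changed over time. Entry requires a facial pain score of at least 4, so both arms may improve through regression to the mean and natural recovery, and a paired test cannot separate that from treatment. The trial's stated objective is EA compared with medication. The baseline significance tests examine differences that, after proper randomisation, can only be due to chance, and the article attaches no adjustment to their result.

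**Working it through.** **Inputs from the article.** 62 patients per group and a 20% dropout rate (Sample size estimation); two-sided 5% tests (Statistical analysis); rates of 91% and 74.4% for the binary measure (Sample size estimation). The article gives no precision figure for a score comparison, so there is none to reproduce.

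**Assumptions.** The article does not give the baseline-to-follow-up correlation r; 0.3 to 0.6 is assumed. It gives no target difference for scores either; 0.5 SD is assumed.

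**Evaluable patients.** 62 × (1 − 0.20) = 49.6, taken as 50 per arm.

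**Variance of the treatment comparison**, relative to a t-test on follow-up scores = 1, with equal variances at the two times:

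- t-test on change scores: 2(1 − r)
- ANCOVA: 1 − r²

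| r | Change-score t-test | ANCOVA | Equivalent n per arm, 50/(1 − r²) | ANCOVA power at 0.5 SD |
|---|---|---|---|---|
| 0 | 2.00 | 1.00 | 50 | 70% |
| 0.3 | 1.40 | 0.91 | 55 | 74% |
| 0.4 | 1.20 | 0.84 | 60 | 77% |
| 0.5 | 1.00 | 0.75 | 67 | 82% |
| 0.6 | 0.80 | 0.64 | 78 | 87% |

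The r = 0 row of the ANCOVA columns is the unadjusted follow-up-score t-test. Power is from the non-central t distribution with 50 per arm and a standardised difference of 0.5/√(1 − r²).

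**Against follow-up scores.** The variance falls by r²: 9% at 0.3, 36% at 0.6. The difference detectable with 80% power falls from 0.566 SD to 0.490 SD at r = 0.5 (0.566 × √0.75 = 0.490).

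**Against change scores.** The ratio is (1 − r²)/[2(1 − r)] = (1 + r)/2, which is 0.65 at r = 0.3 and 0.80 at r = 0.6. ANCOVA is therefore more precise under this reading too.

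**Binary measure (VAS of 2 or less at week 4).** A simulation used 1,500 trials of 50 per arm, rates of 91% and 74.4%, and a latent normal score correlated r with baseline. It compared an uncorrected chi-square test with logistic regression adjusted for baseline:

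| r | Chi-square | Adjusted logistic |
|---|---|---|
| 0.3 | 63.6% | 64.5% |
| 0.5 | 62.0% | 68.3% |

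The gain is 0.9 and 6.3 points.

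**How many covariates the binary model can bear.** Expected non-responders are 50 × 0.09 + 50 × 0.256 = 4.5 + 12.8 = 17.3. With arm, baseline and centre in the model, that is 17.3/3, or fewer than 6 per term.

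**The case against.** The strongest reply is that this is a matter of efficiency and not an error, and that the larger figures belong to the wrong endpoint. Much of it stands.

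- **Validity.** Randomisation keeps the unadjusted tests valid. A reader might infer that the treatment estimate is biased; it is not.
- **Endpoint.** The sample size section defines the primary metric as the share with VAS of 2 or less at week 4, and a share falls under the chi-square rule. The 74 to 87% power figures do not apply to it. They describe VAS as a score, which is the primary outcome in the abstract and the outcome section, and the secondary scales.
- **Skewness.** If some 74 to 91% of patients score 2 or less on a 0 to 10 scale, week-4 VAS may pile up near zero, and the plan's own rule would then choose a rank test. The t-test arithmetic would be only a guide, and floors at entry and follow-up could lower the correlation.
- **Wording.** A reader might infer that baseline scores are discarded, or that testing is visit by visit. The article says neither. It does not state whether follow-up or change scores are compared, and with change scores baseline does enter the comparison. The precision argument holds either way.
- **Paired and baseline tests.** A reader might infer that efficacy will be claimed from significance in one arm alone. The article does not say so; it keeps a separate between-group test. Nor does it say that baseline p-values will drive any decision.
- **Centre.** No stratification by centre is described, so the design does not compel adjustment for it.

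The reply that covariates may sit in an unseen analysis plan carries less weight. The article does not leave the tests open: it names them, and a baseline-adjusted model would replace that text.

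**Conclusion.** The point holds as a loss of precision that can be avoided at little cost. For continuous scores the loss is modest at a correlation of 0.3 (9% of variance, 4 points of power) and substantial at 0.5 or above (25% or more of variance, at least 12 points of power). These figures rest on the assumed correlation, the assumed 0.5 SD difference, 50 evaluable patients per arm and roughly normal scores. For the binary measure the gain is about 1 to 6 points at correlations of 0.3 to 0.5, under a latent-normal assumption.

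The direction does not depend on the reading of the t-test: for any correlation between 0 and 1, ANCOVA has lower variance than either version. The change should be made, but the trial's comparison would not be invalid without it.

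**What to change.** - For VAS and each scale, make the between-group comparison an ANCOVA at week 4, or a mixed model over visits, with the baseline score as covariate. Report the adjusted difference with a 95% CI. Centre may be added as a covariate. Because the Elimination criteria remove withdrawals and losses from the analysis, a mixed model would gain little from partial data as matters stand, so ANCOVA is the simpler choice.
- If the share with VAS of 2 or less is the primary outcome, keep the chi-square test or use a risk difference adjusted for baseline VAS, with few covariates because non-responders will be few. The article's two definitions of the primary outcome need to be reconciled before the primary model can be fixed.
- Describe baseline data by group without p-values.
- Label within-group paired t-tests as descriptive, and say that they are not evidence on EA versus pregabalin.

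**Cost.** No new data are needed. There is slightly more analysis work, and ANCOVA brings a model assumption that skewed scores may strain, so a rank-based check for such scores would be sensible.
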